# Mobile Intervention to Address Cannabis Use Disorder Among Black Adults: Protocol for a Randomized Controlled Trial

**DOI:** 10.2196/52776

**Published:** 2024-02-19

**Keywords:** cannabis use, false safety behaviors, mobile health, just-in-time adaptive interventions, Black or African American, mobile phone, African American, Black, cannabis, adults, adult, Hispanic, Latin, adaptive intervention, cannabis reduction, cessation, ecological momentary assessments

## Abstract

**Background:**

African American or Black (hereafter referred to as Black) adults who use cannabis use it more frequently and are more likely to meet criteria for cannabis use disorder (CUD) than both White and Hispanic or Latin individuals. Black adults may be more apt to use cannabis to cope with distress, which constitutes a false safety behavior (FSB; a behavior designed to reduce psychological distress in the short term). Although FSB engagement can perpetuate the cycle of high rates of CUD among Black individuals, limited work has applied an FSB elimination treatment approach to Black adults with CUD, and no previous work has evaluated FSB reduction or elimination in the context of a culturally tailored and highly accessible treatment developed for Black individuals.

**Objective:**

This study aims to develop and pilot-test a culturally tailored adaptive intervention that integrates FSB reduction or elimination skills for cannabis reduction or cessation among Black adults with probable CUD (Culturally Tailored-Mobile Integrated Cannabis and Anxiety Reduction Treatment [CT-MICART]).

**Methods:**

Black adults with probable CUD (N=50) will complete a web-based screener, enrollment call, baseline assessment, 3 daily ecological momentary assessments (EMAs) for 6 weeks, and a follow-up self-report assessment and qualitative interview at 6 weeks after randomization. Participants will be randomized into 1 out of the 2 conditions after baseline assessment: (1) CT-MICART+EMAs for 6 weeks or (2) EMAs only for 6 weeks.

**Results:**

The enrollment started in June 2023 and ended in November 2023. Data analysis will be completed in March 2024.

**Conclusions:**

No culturally tailored, evidence-based treatment currently caters to the specific needs of Black individuals with CUD. This study will lay the foundation for a new approach to CUD treatment among Black adults that is easily accessible and has the potential to overcome barriers to treatment and reduce practitioner burden in order to support Black individuals who use cannabis with probable CUD.

**Trial Registration:**

ClinicalTrials.gov NCT05566730; https://clinicaltrials.gov/study/NCT05566730

**International Registered Report Identifier (IRRID):**

DERR1-10.2196/52776

## Introduction

Cannabis has been among the most widely used substances for 30 consecutive years in the United States [1], and rates of past-year use have consistently increased in the general population [2,3]. Among individuals who use cannabis, African American or Black (hereafter referred to as Black) individuals exhibit more severe use patterns, including weekly use, and are more likely to meet diagnostic criteria for current cannabis use disorder (CUD) than both White and Hispanic or Latin individuals who use cannabis [4-6]. These data are alarming as CUD is associated with more severe psychosocial risk profiles relative to cannabis users without CUD and nonusers, including poly-substance use, psychiatric problems, and legal trouble [7]. Additionally, although Black individuals who use cannabis are more likely to report being ready to quit and making a recent quit attempt than both Hispanic or Latin and White individuals who use cannabis [8,9], this population is less likely to seek in-person treatment relative to White individuals who use cannabis. Specific individual (eg, beliefs about use) [10], community (eg, neighborhood attitudes about use) [11], and institutional (eg, health care access) [12] factors, as well as institutionalized racism and discrimination (eg, more likely to not be listened to by practitioners) [13], likely contribute to the reluctancy to seek traditional treatments among Black individuals with CUD. Given that treatment involvement has been shown to assist with cannabis use reduction and prolonged abstinence [14], addressing the lack of treatment engagement among this population is imperative to reduce the potential negative health and psychological effects of cannabis use among this group.

Psycho-sociocultural models of substance use posit that Black individuals may use cannabis and continue using it despite cannabis-related problems to manage psychological distress associated with minority-related stress and daily stressors [15-18]. Using cannabis to cope with such distress reflects a false safety behavior (FSB), or a behavior designed to reduce psychological distress in the short term but paradoxically maintains or even exacerbates distress in the long term [19,20]. FSB is more frequent among Black individuals compared to non-Hispanic or Latin White individuals and it is associated with more anxiety, depression, and suicidal thoughts and behaviors among Black individuals [21]. Thus, FSB is an important behavioral vulnerability factor associated with mental health problems among Black individuals. These findings are concerning as problematic cannabis use is higher among those with mental health problems [22], and mental health problems interfere with changing cannabis use [23]. Moreover, the majority of individuals who use cannabis tend to engage in additional FSBs such as avoidance and avoiding social situations when cannabis is unavailable [24], and FSBs may contribute to cannabis-related problems due to tendencies to engage in maladaptive attempts to regulate negative affect [25]. As such, FSB engagement can perpetuate the cycle of high rates of CUD among Black individuals who use cannabis and increase the risk for poor psychosocial outcomes and cannabis-related disparities [24,26,27].

Importantly, transdiagnostic treatments have been developed to eliminate FSBs to improve behavioral health outcomes. Specifically, cognitive-behavioral approaches to FSB elimination treatment that target the identification and elimination of FSBs have been designed and successfully used for use across various anxiety disorders [20]. Furthermore, recent work has explored the potential of FSB elimination integrated with motivation enhancement therapy combined with cognitive behavioral therapy (MET-CBT) to address the co-occurrence among anxiety and CUDs, Integrated Cannabis and Anxiety Reduction Treatment (ICART) [28-30]. In a pilot test of ICART, individuals with CUD were randomized to either in-person ICART or MET-CBT for CUD [28]. Although participants in both study groups reported decreased cannabis use and related problems, patients in the ICART condition were more likely to be abstinent posttreatment than those in the MET-CBT condition. Patients with more severe baseline cannabis use and use-related problems were especially likely to benefit from ICART [31]. These findings suggest that integrating FSB elimination with MET-CBT is at least as efficacious, if not more efficacious, as a gold-standard psychosocial CUD treatment (MET-CBT), especially for patients with more severe cannabis-related pathology.

Despite the potential for FSB reduction or elimination treatments to assist with cannabis use reduction or cessation among individuals with problematic use, this work has been limited by its in-person design and lack of cultural tailoring to Black adults. Indeed, given the cannabis-related and FSB disparities experienced by Black adults [16,21], it may be beneficial to evaluate FSB reduction or elimination integrated with cognitive behavioral therapy (CBT) for CUD in the context of a culturally tailored and highly accessible treatment (ie, a mobile health [mHealth] intervention delivered via a smartphone app) developed for this underserved group.

Extant literature has highlighted existing mHealth work for cannabis use and CUD [32], including mHealth interventions that have been culturally tailored to treat specific populations such as individuals with psychosis [33], as well as individuals with comorbid CUD and cigarette smoking [34]. However, no mHealth interventions for cannabis use and CUD currently target specific psycho-sociocultural factors related to cannabis use and use-related problems among Black individuals who use cannabis with probable CUD. We have therefore developed and are currently pilot-testing a culturally tailored intervention for Black adults with probable CUD through integrated FSB reduction or elimination with CBT for CUD (Culturally Tailored-Mobile Integrated Cannabis and Anxiety Reduction Treatment [CT-MICART]) using an accessible, adaptable, and highly scalable smartphone app. The goal is to examine the effects of CT-MICART on cannabis use, coping motives for cannabis use, and FSB engagement. We hypothesize that participants who are randomized into the CT-MICART condition will report better cannabis outcomes and less FSB compared to those who are randomized into the control condition at the 6-week follow-up. Furthermore, we will examine app engagement indicators and review qualitative data for methods to improve app content.

## Methods

### Ethical Considerations

All participants provided written informed consent signed electronically after reviewing consent documents with research staff. To protect participant privacy and confidentiality, all phone and Zoom (Zoom Video Communications) appointments are completed by trained research staff in a secure office. Additionally, participants are assigned an ID number that is used to identify their data throughout the study. Only trained research staff have access to the key that can match the participant data to the participant’s name. The key is password-protected on a secure server housed at the University of Houston. Participants are compensated up to US $160 in Amazon electronic gift cards for participating in the study. The institutional review board (IRB) at the University of Houston approved the study (STUDY00003690).

### Study Design

A total of 50 Black adults with probable CUD are being recruited through national advertisements across different social media and web-based platforms to participate in this study. Eligible participants are randomized into 1 out of the 2 conditions (ecological momentary assessment [EMA] only vs CT-MICART+EMA). All the participants who consented are asked to complete 3 prompted daily EMAs for 6 weeks. Only participants in the CT-MICART+EMA condition will receive intervention content. Participants are informed during the consent process that they have an equal chance of being assigned to each study condition. Moreover, participants are also informed that one of the study’s treatment conditions consists of watching treatment videos and using CT-MICART app features, while the other condition consists only of completing daily EMAs. Following the 6-week intervention period, all participants will complete a follow-up assessment survey in the app and a qualitative interview phone call. See Figure 1 for the study flow.

**Figure 1 figure1:**
[figure not shown]
Study flowchart. CT-MICART: Culturally Tailored-Mobile Integrated Cannabis and Anxiety Reduction Treatment; EMA: ecological momentary assessment.

### Participants

Participants will include 50 individuals who identify as Black with probable CUD. Participants must meet the following eligibility criteria to participate: (1) at least 18 years of age, (2) self-identify as Black or African American, (3) meet criteria for probable CUD (assessed via the Cannabis Use Disorder Identification Test-Revised [CUDIT-R] with a score of >12) [35], (4) motivated to reduce cannabis (>5 on a 10-point scale), (5) score ≥4 on the Rapid Estimate of Adult Literacy in Medicine-Short Form (REALM-SF) indicating higher than sixth-grade English reading level [36], (6) own an Android smartphone for EMA completion, and (7) report cannabis use to manage anxiety or stress in the past month. Exclusion criteria include (1) legal mandate of substance misuse treatment; (2) report of current or intended participation in a concurrent substance use treatment, including pharmacotherapy or psychotherapy for CUD not provided by the researchers; (3) ongoing psychotherapy of any duration directed specifically toward the treatment of anxiety or depression; (4) not being fluent in English; (5) pregnant or planning to become pregnant within the next 6 months (assessed via self-report); and (6) inability to provide a photo ID and valid address to verify identity.

### Procedures

This study is funded by the National Institute on Minority Health and Health Disparities (U54MD015946) and is registered on ClinicalTrials.gov (NCT05566730). The IRB where the study takes place has reviewed and approved all procedures and study materials. Interested participants are asked to complete a web-based self-report screener survey via Qualtrics (Qualtrics International Inc). Those deemed eligible at the screener are then scheduled for an enrollment Zoom call of approximately 30 minutes. During the enrollment Zoom call, participants are given detailed information on the goals, purpose, and procedures of the study; provide informed consent; show their photo ID to the research team; and complete a literacy test to confirm they are at higher than sixth-grade English reading level [37]. Those found eligible during the enrollment Zoom call are asked to download the Insight smartphone app onto their personal smartphone and to complete the 30-minute baseline survey via the app. Eligible participants who complete the baseline survey are then contacted by research staff so they can be randomized into a study condition (ie, CT-MICART vs EMA only). During this randomization call, participants are oriented to app features for their assigned condition by the research team.

Following randomization, participants are prompted by the app to complete 3 EMAs daily. EMAs take approximately 2-3 minutes to complete. The research staff monitors the EMA completion rates of each participant on a weekly basis. When a participant’s completion rate falls below 80%, a research staff member contacts the participant via text, phone, or email to remind them of the importance of completing their daily EMAs. Participants are informed that they can contact study staff at any point during the study by pressing the “Call Staff” button at the top of the app screen should they experience technical difficulties. Please see Figure 2 for a screenshot of the CT-MICART features available via the app home screen.

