### Assessments

#### Overview

See Table 1 for a schedule of data collection and measures list. All measures have been used among samples of Black adults.

**Table 1 table1:** Measures and schedule for data collection.

Measure name	Screener	Baseline	6-week follow-up	EMA^a^ items
Demographics or background information	✓			Cannabis use assessment (outcomes)
Motivation to quit cannabis (eligibility)	✓			Alcohol consumption
REALM-SF^b^ (eligibility)	✓			Motivation regarding cannabis use
CUDIT-R^c^ (eligibility)	✓		✓	Watch treatment videos (CT-MICART^d^ condition only)
Legal mandate status (eligibility)	✓			Cannabis use goal assessment (CT-MICART condition only)
Report of cannabis use to manage anxiety or stress in the past month (eligibility)	✓			Negative affect
Assessment of ongoing substance use treatment or anxiety and depression (eligibility)	✓			Confidence in reducing or quitting
Safety Aid Scale (outcome)		✓	✓	Urges or cravings
Qualitative interview (outcome)			✓	Social support and daily interactions
System Usability Scale (outcome)			✓	Coping motives for cannabis and consequences or benefits of using
Credibility or Expectancy questionnaire (outcome)		✓	✓	False safety behavior elimination engagement
Marijuana Motives Measure (outcome)		✓	✓	N/A^e^

^a^EMA: ecological momentary assessment.

^b^REALM-SF: Rapid Estimate of Adult Literacy in Medicine-Short Form.

^c^CUDIT-R: Cannabis Use Disorder Identification Test.

^d^CT-MICART: Culturally Tailored-Mobile Integrated Cannabis and Anxiety Reduction Treatment.

^e^N/A: not applicable.

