#### Daily EMAs

Throughout the 6-week intervention period, participants complete 3 daily EMAs occurring at specific times (one 30 minutes after self-selected wake time, one 60 minutes before the self-selected sleep time, and one at 12:15 PM). Items include questions about cannabis use, duration of being high, urges or cravings, motivation, and confidence to reduce or quit cannabis, negative affect, social support, and other substance use. Each EMA also gauges the CT-MICART+EMA participants’ cannabis goal for the day (ie, wanting to avoid using cannabis today, reduce use today, or no cannabis use goal today). All participants are also instructed to access the app’s on-demand assessment features, including the “Record Stress or Urge,” “I’m About to Use,” and “I just used” buttons, when they experience increased stress or an urge to use cannabis as well as anytime they think they might use or after actual cannabis use. Each time participants click these buttons, they are asked to complete a brief set of questions pertaining to their current situation.

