#### Hypothesis Testing

##### Overview

We will examine treatment effects on cannabis use (derived from EMA data) using multilevel models. We will focus on two cannabis use outcomes: (1) use on a given day and (2) frequency of use within a given day. We will account for baseline covariates and time since the start of the intervention. We will also use appropriate random effects and residual constraints. For coping motives for cannabis and FSB engagement, we will conduct a linear regression analysis wherein we will regress treatment condition on each outcome assessed at the 6-week follow-up while adjusting for baseline scores of the specific outcome and baseline covariates. Triangulation mixed methods quantitative or qualitative data analysis [43] will be used to evaluate quantitative and qualitative data.

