## Discussion

### Principal Findings

Black adults evince significant cannabis-related health disparities compared with non-Black populations [13,15,51]. Thus, the primary goal of this study is to develop and pilot-test a culturally adapted mobile app for Black adults with probable CUD to help mitigate these disparities. We have culturally tailored this mobile intervention following the Cultural Accommodation Model [38], incorporating knowledge from the current research team, published literature, expert opinion, and feedback from the CRAB. As a next step, we seek to obtain data on the initial efficacy and qualitative evaluation of the app with the target population (ie, Black adults with probable CUD). To our knowledge, this is the first culturally tailored mHealth intervention to integrate FSB and CBT for CUD for Black adults with a probable CUD. We hypothesize that the culturally tailored mobile app CT-MICART will lead to reduced cannabis use and related problems and reduce the use of FSBs.

Though extant literature has highlighted existing mHealth work for cannabis use and CUD [32], including mHealth interventions tailored to treat specific populations (ie, individuals with psychosis and comorbid substance use) [33,34], this study is the first to target specific psycho-sociocultural factors related to cannabis use and use-related problems among Black cannabis users through a mobile intervention. Should the CT-MICART app prove efficacious in reducing cannabis use, it will provide health care officials and researchers a unique opportunity to further refine and provide low-cost and easily accessible treatment for a historically underrepresented and underserved population. The success of the CT-MICART app would also provide the foundation to further refine and culturally inform better implementation of the app through qualitative interviews of all participants. Overall, the CT-MICART app and its development provide the potential to address the dearth of literature that exists for mobile health development and Black individuals who use cannabis.

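### The EMA cannabis-use outcomes have no pre-randomization value on the same scale, so change from before treatment cannot be estimated and the between-arm estimate loses precision

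*Protocol article*

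**What the plan says.** - **Source of the outcomes.** Hypothesis Testing, Overview: "We will examine treatment effects on cannabis use (derived from EMA data) using multilevel models". Two outcomes are named: ("1) use on a given day and (2) frequency of use within a given day").
- **When EMAs run.** Procedures: "Following randomization, participants are prompted by the app to complete 3 EMAs daily". Daily EMAs: "Throughout the 6-week intervention period, participants complete 3 daily EMAs occurring at specific times". The baseline survey is completed before the randomization call, and no EMA run-in is described.
- **What is scheduled before randomization.** In Table 1 the entry "Cannabis use assessment (outcomes") appears only in the column of EMA items. The Baseline column is ticked for the Safety Aid Scale, the Credibility or Expectancy Questionnaire and the Marijuana Motives Measure. The CUDIT-R is ticked at the screener and again at 6 weeks. The Study Screening and Demographics Questionnaire section adds that the screener asks about earlier substance use, without giving the items.
- **What is adjusted for.** In Hypothesis Testing, the regressions for coping motives and FSB adjust for the baseline score of the outcome concerned. The cannabis-use models adjust for unnamed baseline covariates and elapsed time.
- **The hypothesis.** The Introduction frames it as better cannabis outcomes than control at 6 weeks. Principal Findings says the app "will lead to reduced cannabis use and related problems and reduce the use of FSBs".

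**The concern.** The outcomes listed first in the Introduction and in Hypothesis Testing are the ones without a baseline value, while the outcomes listed after them have one. No primary outcome is named, so calling cannabis use the leading outcome is a reading of that order.

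The first EMA days cannot serve as a baseline. By then the active arm has been oriented to its app features and is receiving messages and on-demand content.

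Three things are at stake:

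- The check of group equivalence promised in the General Overview of Data Analysis cannot include the outcome itself.
- The Limitations section concedes that self-monitoring might help the EMA-only arm. Without a pre-treatment level, a null result on these outcomes cannot distinguish two arms that both improved on entry from two arms that did not change.
- The General Overview says conclusions will rest on effect sizes and confidence intervals that guide later trials. Interval width is therefore the main product of this pilot, and a baseline covariate is an inexpensive way to narrow it.

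**Working it through.** The protocol gives no alpha, power, effect size or SD for its sample size, so there is no figure of its own to reproduce. What follows is an illustration.

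**Inputs from the protocol article**
- Sample size, from Study Design: "A total of 50 Black adults with probable CUD are being recruited through national advertisements".
- Allocation, from Study Design: participants are told that "they have an equal chance of being assigned to each study condition". This gives about 50 / 2 = 25 per arm.

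**Assumptions**
- One continuous value per person, in SD units. The planned outcomes are daily any-use and within-day frequency over six weeks, so this is a simplification.
- Full follow-up, and a two-sided 95% interval with the normal approximation.
- r is the correlation between a baseline use measure and the outcome. The protocol gives no value; 0 to 0.7 is shown.

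**Step 1: chance imbalance at entry.** The SD of the difference in baseline means is sqrt(2/25) = 0.283 SD. P(|difference| > 0.3 SD) = 2 × (1 − Φ(0.3/0.283)) = 0.29. P(|difference| > 0.5 SD) = 0.08. This is ordinary sampling variation with mean zero, and the unadjusted confidence interval already carries it.

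**Step 2: interval width with a baseline covariate.** Half-width = 1.96 × sqrt(1 − r²) × sqrt(2/25). Equivalent unadjusted sample = 50/(1 − r²).

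| Assumed r | sqrt(1 − r²) | 95% CI half-width (SD) | Narrower by | Equivalent total N |
|---|---|---|---|---|
| 0 | 1.000 | 0.55 | – | 50 |
| 0.3 | 0.954 | 0.53 | 5% | 55 |
| 0.5 | 0.866 | 0.48 | 13% | 67 |
| 0.7 | 0.714 | 0.40 | 29% | 98 |

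**Step 3: gain over a proxy already in the model.** Suppose a screening measure alone reaches 0.3, and adding a same-scale baseline raises the multiple correlation to 0.5 or 0.7. The width ratio is sqrt(0.75/0.91) = 0.91 or sqrt(0.51/0.91) = 0.75. The extra gain is then about 9% or 25%, instead of 13% or 29%.

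**Step 4: what can and cannot be estimated on the EMA outcomes**

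| Quantity | Available? |
|---|---|
| Difference from control in use | Yes, by randomization |
| Trend within an arm over the six weeks | Yes, through the time term |
| Change from before treatment | No |
| Balance at entry on the outcome itself | No |

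**The case against.** **The comparison does not need a baseline.** A reader might infer that the hypothesized reduction cannot be shown at all. The documents do not support that. The Introduction states the hypothesis against control, Hypothesis Testing analyzes treatment effects, and the sentence in Principal Findings can be read as the same causal contrast. Randomization makes a reduction relative to control estimable without a baseline. This part of the objection stands in full. Equally, chance imbalance is no separate threat on top of the confidence interval, and within-arm trends after the start can still be described.

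**Proxies exist.** The CUDIT-R is collected before randomization and repeated at 6 weeks, and the screener asks about earlier substance use. Nothing bars either as a covariate, and the planned equivalence check could include them. This stands in part. Neither is named as a covariate. The CUDIT-R is described as gauging the likelihood of cannabis use disorder, and its range is cut by the entry threshold. The content of the substance-use items is not given. The Marijuana Motives Measure section mentions frequency of use loosely, but describes a motives questionnaire and does not establish a count of use.

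**An article condenses.** Item-level detail may sit in the full protocol, so the screener may contain a frequency item. That is possible, and the fix below allows for it. It does not change the start of the EMAs, which the article states outright, or the absence of any EMA-scale value before that point.

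**The gain is assumed.** The larger gains depend on r of 0.5 to 0.7 and compare with no covariate. At r = 0.3 the half-width moves only from 0.55 to 0.53 SD. This stands, and it is why a range is given.

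**Conclusion.** The point holds as a matter of precision and interpretation, not of validity. The schedule yields no pre-randomization value of the EMA cannabis-use outcomes on their own scale. Change from before treatment cannot be estimated on them, and balance on the outcome cannot be checked.

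The cost in precision is a half-width of 0.55 SD where 0.53 to 0.40 SD might have been had. That rests on 25 per arm, a single continuous value per person and an assumed r of 0.3 to 0.7. It is smaller if a screening proxy is adjusted for. For a self-described underpowered pilot this is a moderate, cheaply avoidable loss.

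**What to change.** **For this trial.** The Results section says enrollment ended in November 2023, so new baseline items are no longer possible. Two changes remain open:

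1. Prespecify, before the outcome data are analyzed, one cannabis measure already collected at screening as a covariate in both EMA models. Use the CUDIT-R score, or the earlier-substance-use items if they capture cannabis frequency. Include it whether or not the arms differ on it.
2. State the effect on use as a difference from control, not as a reduction from baseline, and list the missing pre-treatment value under Limitations.

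The cost is one model term and a few sentences. A proxy will recover only part of the precision.

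**For the next trial, by design.** Add past-7-day days of use and occasions per using day to the in-app baseline survey and to the Baseline column of Table 1, worded as in the EMA. Use them as covariates in both EMA models. The cost is a few items in a survey that already takes 30 minutes; the drawback is that recall differs in mode from momentary reporting. Pre-randomization EMA days would avoid that difference, but they add burden and self-monitoring in both arms and need a defined interval before the randomization call.
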